### Outcomes

#### Primary outcome

The primary outcome is the between-group difference in the four metre walk speed at 4 months. The four metre walk speed is performed from a standing start, with the participant asked to walk at their usual pace. Short-course walking speed is a powerful predictor of a range of adverse outcomes in older people, including death, dependency and cognitive impairment.^33–35^ The 4 m walk speed has been used as an outcome measure in previous trials, including those of metformin^30^ and the minimum clinically important difference for this measure has been estimated to be 0.1 m/s.^28^

#### Secondary outcome measures

Secondary outcome measures in the MET-PREVENT trial include other measures of physical performance, health-related quality of life, mechanistic outcomes and outcomes related to trial performance. Maximum handgrip strength will be measured using a Jamar dynamometer^36^; three readings will be taken for each hand and the highest reading used. A 6 min walk distance will be recorded over a 10 m course with standardised encouragement.^37^ The Short Physical Performance Battery (SPPB)^38^ will be measured as a composite test of lower limb function with the five-times sit to stand time performed as part of the SPPB analysed as an additional, separate outcome. Lean body mass will be estimated using the Akern 101 bioimpedance system (Akern, Pontassieve, Italy), with the Sergi equation used to derive measures of total lean body mass.^39^ The number of physical frailty characteristics (0–5) and the components of the score, and transitions between robust (0 characteristics), physical prefrailty (1–2 characteristics) and physical frailty (3+ characteristics) will be recorded.

Generic health-related quality of life will be recorded using the EuroQoL 5 dimension 5 level (EQ5D-5L) and Short-Form 36 (SF-36) (Physical and Mental Component Summary Scores) questionnaires.^40 41^ Instrumental activities of daily living (ADLs) will be recorded using the Nottingham extended activities of daily living (NEADL) score.^42^ Glycosylated haemoglobin will be measured along with the homeostatic measure of insulin resistance (HOMA-IR) derived from peripheral glucose and insulin measures.^43^ Advanced glycosylation end-products (AGE) presence in the skin will be measured by auto fluorescence using the AGE Reader (Diagnoptics, Gronigen, Netherlands).^44^ Blood samples will be processed and stored for later mechanistic studies, including measurement of a panel of proinflammatory cytokines and markers of cellular senescence and oxidative stress. Stool samples will be collected and stored for later microbiome studies. Metrics describing the conversion rate from screening to randomisation, and the retention rate of recruited participants over their 4-month study participation will also be collected.

### Participant timeline

Participants who express interest in the trial will enter a brief pre-screening process by telephone to check provisional eligibility. Verbal consent will be sought for the prescreen process, including access to medical records for further review of suitability for the trial. At prescreening, participants are asked if they have a diagnosis of diabetes mellitus, are taking metformin, or have previously been intolerant of metformin. The Strength, Assistance, Rise, Climb, Falls (SARC-F) questionnaire will be administered^45^; this comprises five questions on physical function with a score between 0 and 10. Based on previous data,^46^ a score of 1 or more will be sufficient to identify those more likely to have sarcopenia and will enable progression to the screening visit. Participants who pass the prescreen will be given or posted the full participant information sheet (PIS), and all participants will be given at least 48 hours to consider their participation. The PIS can be found in online supplemental appendix 1.

10.1136/bmjopen-2022-061823.supp1Supplementary data

Written informed consent will be obtained at the screening visit, which may take place at home, at clinic or in a research facility. After informed consent is given, information on demographics, medical and medication history and alcohol use will be collected. Maximum handgrip and 4 m walk speed will be measured. Blood will be taken for urea, creatinine and electrolytes (U&Es) and liver function tests (LFTs) unless results are already available from within 3 months prior to the screening visit. Participant eligibility to proceed to the baseline visit is confirmed after the screening visit, once screening assessment results are available.

The schedule of events is given in table 1. Main study outcomes are measured at baseline and the 4-month final visit; safety visits to check renal function, lactate concentrations and AEs take place at 1, 2 and 3 months, and a telephone call takes place 1 week after the baseline visit to ensure that the participant has received and started the study medication.

**Table 1 T1:** MET-PREVENT trial schedule of events

Timepoint	Prescreening	Screen	Baseline	1 week (+3 days) after randomisation	1 month (+1 week) after randomisation	2 months (+1 week) after randomisation	3 months (+1 week) after randomisation	4 months ±2 weeks
Screening, consent and preallocation assessments								
Brief study information sheet and invitation letter posted/given to patients identified via SarcNet Registry, older peoples medicine clinics, day units and rehabilitation facilities and GP practices	X							
Telephone prescreening (verbal consent, demographics, SARC-F tool) for participants who send a positive reply slip	X							
Patient information sheet posted to participants who pass prescreen	X							
Informed written consent		X						
Eligibility assessments (U&Es, LFTs, demographics, medical history, concomitant medication, adverse events, four metre walk speed, 5 x sit to stand time, grip strength)		X						
Eligibility confirmation		X						
Baseline assessments preallocation (blood glucose and HbA1c, height and weight, bioimpedance, AGE skin fluorescence, physical performance tests (SPPB, grip strength, six min walk), quality of life questionnaires (EQ5D5L, SF-36, Nottingham EADL), frailty screening questions (activity, exhaustion).			X					
Allocation (randomisation)—following completion of assessments			X					
Dispensing/posting trial medication			X					
Biological samples								
Blood and stool			X					X
Intervention								
4 months supply of Metformin hydrochloride 500 mg tablets or matching placebo tablets								
Follow-up								
Confirm medication receipt, ability to open medication bottle, date of first dose				X				
Safety blood tests (U&Es, LFTs, glucose, lactate)					X	X	X	X
Adverse event assessments		X	X	X	X	X	X	X
Concomitant Medications		X	X	X	X	X	X	X
Follow-up assessments (blood glucose and HbA1c, weight, bioimpedance, AGE skin fluorescence, physical performance tests (SPPB, grip strength, 6 min walk), quality of life questionnaires (EQ5D5L, SF-36, Nottingham EADL), frailty screening questions (activity, exhaustion).								X
Return of unused trial medication								X
Medication compliance, accountability								X

AGE, advanced glycosylation end; EADL, extended activities of daily living; EQ5D5L, EuroQoL 5 dimension 5 level; GP, general practices; HbA1c, glycated haemoglobin; LFTs, liver function tests; SARC-F, Strength, Assistance, Rise, Climb, Falls; SF-36, short form 36; SPPB, Short Physical Performance Battery; U&Es, creatinine and electrolytes.

### Sample size

Based on previous work, we assumed a minimum clinically important difference for the four metre walk speed of 0.1 m/s.^28^ Assuming a SD of 0.24 as seen in the English Longitudinal Study of Ageing,^47^ and a correlation between baseline and 6-month measures of 0.8, as seen in a recent trial of older people at risk of falls^48^ (a similar population to those who will be enrolled in this trial), a total of 66 participants would be needed (33 per group) to give 80% power to detect this difference at a two-sided alpha=0.05 in an analysis that is adjusted for baseline values. Recruiting 80 participants will allow for 17.5% drop-out (higher than observed in previous trials of spironolactone and of vitamin D in similar populations^49 50^) to give 66 participants at follow-up.

### Recruitment

Recruitment will take place over ten months and participants will be followed up for 4 months; recruitment started in September 2021. Potential participants for MET-PREVENT will be identified by four routes. The SarcNet Registry^31^ contains details of participants who have had grip strength and walk speed measured previously and have consented to be recontacted with offers to participate in other studies. The NIHR BioResource Centre Newcastle registry contains details of participants who have previously given consent for recontact with information about potential trial opportunities suitable for them (REC REF: 18/NE/0138). Participants will also be sought via Older Peoples Medicine Clinics, Day Units, assessment units and rehabilitation facilities in participating centres. Where available, existing information on handgrip strength and walk speed held in the clinical record will be used to identify potential participants. Finally, potential participants will be identified via screening of GP lists, in collaboration with the NIHR Primary Care Research Network. Where interrogation of the electronic FI (eFI) is possible,^51^ invitations will be targeted to those with at least mild frailty denoted by an eFI of 0.12 or greater.

Potentially eligible participants will be sent or given a brief study information sheet, an invitation letter with a reply slip and a prepaid envelope to express interest. The reply slip will be returned to the central study team, who will pass on details to the site recruiting teams. Those who are interested will be contacted for prescreening as described below.

### Assignment of intervention

Participants will be randomised on a 1:1 basis using an interactive web-based randomisation system (Sealed Envelope). Minimisation (with a 30% random element) will ensure balance across the two arms based on the following stratification variables: sex and baseline walk speed (≤0.6 or >0.6 m/s). The allocation sequence is prepared by Sealed Envelope and is concealed from the study team. Participants are allocated a pack number at randomisation; this pack number is used by the trial pharmacy to dispense prelabelled medication packs. Participants, the clinical team and the study team (including investigators, research nurses collecting outcomes data, senior statistician and trial manager) are blind to treatment allocation during the trial. For the independent data monitoring committee (IDMC), the statisticians preparing the report will be partially blind. This means that analysis will be conducted by arm, but the statisticians will not know the treatment allocation for each arm. They will become unblinded if the IDMC requests fully unblinded data. The randomisation system has functionality for emergency unblinding. This will only occur for valid medical or safety reasons where it is necessary for the treating clinician to know which treatment the participant has been receiving; the randomisation system is able to inform the treating clinician by email without unblinding other members of the study team or the participant.

### Data collection and management

The trial schedule of events is presented as a flow diagram (figure 2) and a table of trial processes (table 1). Recruited participants will be followed up for 4 months from the point of randomisation. Data including the number of participants identified, approached, prescreened and screened will be collected and documented on a site screening log. Data will be handled, computerised, stored and archived in accordance with the General Data Protection Regulation (2018), and the latest Directive on GCP (2005/28/EC). Patient identifiable data will remain at each site and will not be collected as part of the trial dataset. Patient identification on data collection tools used will be through a unique sequential screening number allocated by site staff. Data will be transcribed by site staff from data collection worksheets to the trial’s secure, password-limited, validated database (Sealed Envelope, London, UK). The participant trial record, including completed paper data collection tools, will be archived at site for 15 years following the end of the trial. Newcastle Clinical Trials Unit (NCTU) staff monitor trial conduct and data integrity; this is detailed in a Data Management Plan and a Monitoring Plan approved by the trial Sponsor.

**Figure 2 F2:**
[figure not shown]
MET-PREVENT trial flow diagram. EADL, extended activities of daily living; EQ5D-5L, EuroQoL 5 dimension 5 level; GPs, general practice; HbA1c, glycated haemoglobin; LFTs, liver function test; SF-36, Short Form 36; SPPB, Short Physical Performance Battery; U&Es, creatinine and electrolytes.

### Statistical analysis

A statistical analysis plan will document the planned analyses and will be finalised prior to database lock at the end of the trial. For the primary outcome (4 m walk speed at 4 months postrandomisation), the difference between arms will be tested through fitting a linear regression model that is adjusted for baseline four metre walk speed and sex. A suitable transform of the data (eg, the best fitting Box-Cox transform) will be applied to ensure the data are approximately normally distributed. The model will allow estimation of the difference between arms together with the 95% CI and p value for testing the null hypothesis of no difference. Continuous secondary endpoints will be analysed in a similar manner to the primary outcome. Binary secondary endpoints will be analysed with a logistic regression model. All models will be adjusted for the outcome under test at baseline, baseline 4 m walk speed and sex.

The following preplanned subgroup analyses will be performed for the primary outcome: age >75 years vs≤75 years, men versus women, baseline walk speed >0.6 m/s vs ≤0.6 m/s. In addition, a per-protocol analysis will be performed in participants with adherence to study medication ≥80%.

The primary analysis will be a complete-case analysis. In the event the mortality rate is >5%, we will perform a sensitivity analysis by imputing the worst score possible for the primary outcome (ie, 0 m/s) in participants who died before the 4-month visit. A further sensitivity analysis will be performed by imputing the primary outcome to the worst score possible in the event both mortality and withdrawal due to illness is >5%. If more than 10% of primary outcome data is missing after imputation for missing-ness due to death and withdrawal due to illness, a sensitivity analysis using multiple imputation via chained equations using the baseline covariates in the imputation model will be performed. Twenty imputed datasets will be used.

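### Walk speed appears to be measured twice before randomisation, but the primary model uses one reading; adding the other is a cheap, modest gain in precision, not the repair of an error

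*Protocol article*

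**What the plan says.** Statistical analysis (protocol article) specifies the primary comparison of 4-month walk speed by "fitting a linear regression model that is adjusted for baseline four metre walk speed and sex": one walk-speed value plus sex.

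Two pre-randomisation readings seem to exist:

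- **Screening (explicit).** Participant timeline says of the screening visit: "Maximum handgrip and 4 m walk speed will be measured". The eligibility row of Table 1 also names the 4 m walk, and Box 1 requires a speed below 0.8 m/s.
- **Baseline visit (inferred).** Participant timeline says: "Main study outcomes are measured at baseline and the 4-month final visit". The baseline row of Table 1 does not name the 4 m walk. It lists SPPB, grip strength and six-minute walk. The 4-month row lists the same tests and must supply the primary outcome, so a repeat walk at the baseline visit is a fair reading.

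Table 1 places allocation after the baseline assessments, so both readings precede randomisation. The article does not say which of them is meant by baseline walk speed in the model, in the minimisation factor (0.6 m/s cut) or in the subgroup that uses the same cut.

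Sample size plans for "80% power to detect this difference at a two-sided alpha=0.05 in an analysis that is adjusted for baseline values", with one baseline value.

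**The concern.** Each walk test is a noisy reading of the same underlying speed. Two readings predict the 4-month value at least as well as one, and usually better. Because both precede randomisation, using both cannot bias the treatment comparison. The trial is small (80 recruited, 66 expected at follow-up) and its planned power has no margin above 80%, so an unused covariate already in the database deserves a look. What is at stake is the width of the confidence interval for the primary comparison. Its validity is not in question.

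**Working it through.** **Inputs from Sample size.** Difference: "we assumed a minimum clinically important difference for the four metre walk speed of 0.1 m/s". SD: "Assuming a SD of 0.24 as seen in the English Longitudinal Study of Ageing". Correlation: "a correlation between baseline and 6-month measures of 0.8". 33 per group at follow-up, two-sided alpha 0.05.

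**Inputs assumed, because the article does not give them.** Screening-to-baseline correlation ρ from 0.80 to 0.95; screening-to-follow-up correlation 0.75 or 0.80; mean speed of 0.7 to 0.9 m/s in the population screened. Baseline is taken to mean the baseline-visit reading.

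**Step 1: reproduce the plan.**
- Residual SD = 0.24 × √(1 − 0.8²) = 0.24 × 0.6 = 0.144.
- n per arm = 2 × (1.960 + 0.842)² × 0.144² / 0.1² = 32.6, rounded up to 33, so 66 in total. This matches.
- 80 × (1 − 0.175) = 66. This matches.
- Power at 33 per arm: 80.5% by normal approximation; 79.3% by noncentral t, allowing for the two covariates.

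**Step 2: add the second reading, ignoring selection.** With correlations b (baseline) and s (screening) to follow-up:

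R² = (b² + s² − 2bsρ) / (1 − ρ²)

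The residual variance, as a fraction of SD², is 1 − R². With one reading it is 1 − 0.64 = 0.36. Example with b = 0.8, s = 0.75, ρ = 0.90: R² = (0.64 + 0.5625 − 1.08) / 0.19 = 0.645, so 1 − R² = 0.355, a fall of 1.3%.

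| s | ρ | 1 − R² | Fall in residual variance | Power (noncentral t) |
|---|---|---|---|---|
| 0.80 | 0.80 | 0.289 | 19.8% | 87.3% |
| 0.80 | 0.90 | 0.326 | 9.4% | 83.0% |
| 0.80 | 0.95 | 0.344 | 4.6% | 81.1% |
| 0.75 | 0.80 | 0.326 | 9.3% | 83.0% |
| 0.75 | 0.90 | 0.355 | 1.3% | 79.8% |
| 0.75 | 0.95 | 0.359 | 0.3% | 79.4% |

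**Step 3: allow for selection on the screening reading.** Eligibility truncates the screening value at 0.8 m/s, which reduces what it adds. I simulated trivariate normal speeds (SD 0.24, correlations as above before selection), kept screening values between 0.1 and 0.8 m/s, and compared the residual variance with the baseline reading alone and with both readings. Ranges are across source means of 0.7 to 0.9 m/s; power is by noncentral t at 33 per arm.

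| s | ρ | Fall in residual variance | Power gain (points) |
|---|---|---|---|
| 0.80 | 0.80 | 11 to 14% | 4.1 to 5.3 |
| 0.80 | 0.90 | 6.5 to 7.5% | 2.5 to 3.0 |
| 0.80 | 0.95 | about 4% | 1.4 to 1.6 |
| 0.75 | 0.80 | 5 to 6% | 1.9 to 2.5 |
| 0.75 | 0.90 | about 1% | 0.3 to 0.4 |
| 0.75 | 0.95 | 0.2 to 0.3% | 0.1 |

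The truncated figures are the relevant ones for this trial.

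**The case against.** The strongest reply is that the plan contains no mistake. Adjustment for one baseline value is standard and valid, it covers both minimisation factors, and it is the analysis the sample size assumed. All of that stands. The article does fix the primary covariates, so the choice is open to comment, but only as a missed efficiency.

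The size of the gain is also open to challenge, and that stands too. At ρ = 0.80 the two pre-randomisation readings would agree no better than the sample size assumes for readings 6 months apart, so the top of the range is an extreme case. If screening is the weaker predictor and the readings agree closely, the gain is close to nil. The untruncated rise from 79% to 87% should not be quoted as the expected benefit.

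Three stronger readings are tempting and unsupported:

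- **That selecting on a slow screening walk biases the result through regression to the mean.** Selection precedes randomisation, so regression to the mean is the same in expectation in both arms.
- **That selection leaves the trial underpowered.** In the simulation the baseline-to-follow-up correlation falls to about 0.58 to 0.69, but the outcome SD shrinks as well (0.18 to 0.20), and power with one reading stays at or slightly above the planned level.
- **That the article states outright that the walk is repeated at the baseline visit.** It does not. The repeat is an inference, though a sound one.

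**Conclusion.** A modest, optional improvement. The plan as written is valid and has about the power it claims. Using both pre-randomisation readings would reduce residual variance by about 0 to 15% and raise power by about 0 to 5.5 points. I consider 1 to 3 points most plausible, on the judgement that the two readings agree closely (ρ of 0.90 to 0.95) and predict follow-up about equally well; with a weaker screening reading the gain would be under half a point. All of this assumes that the walk is repeated at the baseline visit, that the planned SD of 0.24 and correlation of 0.8 describe the population before selection, and that the unstated correlations lie in the ranges above. The missing definition of baseline walk speed is worth settling in any case.

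**What to change.** Before unblinding, and in the statistical analysis plan that the article says will be finalised before database lock:

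1. Specify the primary model as 4-month walk speed on arm, baseline-visit speed, screening-visit speed and sex. Using the mean of the two readings in place of two separate terms is an acceptable alternative.
2. State which visit supplies baseline walk speed for the minimisation factor and for the 0.6 m/s subgroup.
3. Consider the same for grip strength, which Table 1 names at both visits. Extend it to five-times sit-to-stand only if screening values are complete. Eligibility needs either low grip or slow sit-to-stand, and the screening text does not list sit-to-stand although Table 1 does. If some values are missing, the covariate would remove participants from a complete-case analysis.

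The cost is a line or two of text and one degree of freedom (none if the mean is used), with no new visit or measurement. The downside is that the gain may prove negligible.

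### The primary model is committed to a data-chosen normalising transform with no stated reporting scale, so the estimate and CI need not be in the m/s used for the outcome, target difference and power

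*Protocol article*

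**What the plan says.** The Primary outcome section defines the outcome as the difference between arms in four metre walk speed at 4 months and cites an MCID of 0.1 m/s. The Sample size section works on the same scale: "we assumed a minimum clinically important difference for the four metre walk speed of 0.1 m/s"; "Assuming a SD of 0.24 as seen in the English Longitudinal Study of Ageing"; and "a correlation between baseline and 6-month measures of 0.8". These give "a total of 66 participants would be needed (33 per group") for "80% power to detect this difference at a two-sided alpha=0.05 in an analysis that is adjusted for baseline values".

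The Statistical analysis section specifies a linear regression adjusted for baseline walk speed and sex, and then adds: "A suitable transform of the data (eg, the best fitting Box-Cox transform) will be applied to ensure the data are approximately normally distributed". The same model is to supply the difference between arms, its 95% CI and the p value. Continuous secondary endpoints are to be handled similarly.

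The primary analysis is complete-case. If mortality exceeds 5%, a sensitivity analysis is planned by "imputing the worst score possible for the primary outcome (ie, 0 m/s") for participants who died. A further one uses the worst score if both mortality and withdrawal due to illness exceed 5%. A subgroup analysis of the primary outcome splits baseline speed at 0.6 m/s. A separate statistical analysis plan is to be finalised before database lock and is not available here.

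**The concern.** Three features of the transform sentence cause difficulty together.

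- It is a commitment, not a contingency. No condition, such as clearly non-normal residuals, triggers it.
- The transform is chosen from the trial data and judged on the data. The regression assumption concerns the residuals.
- Nothing says on what scale the difference and CI will be reported.

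The trial is meant to give proof of concept for a larger trial, and the Discussion says it is powered for the MCID. Readers will want an effect in m/s with a CI to set beside 0.1 m/s. A coefficient on a power scale fixed only after the data are seen does not provide that. Scale also affects effect modification: a benefit that is constant in m/s is not constant after transformation. The baseline-speed subgroups could then appear to differ for no other reason than the scale.

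**Working it through.** **1. Reproduce the plan's figure.** Inputs from the Sample size section: difference 0.1, SD 0.24, correlation 0.8, two-sided alpha 0.05, power 80%.

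- Residual SD = 0.24 × √(1 − 0.8²) = 0.144.
- n per arm = 2 × (1.960 + 0.842)² × 0.144² / 0.1² ≈ 32.6, so 33 per arm and 66 in total. This matches the plan.
- Power at 33 per arm is 0.805 (normal approximation) or 0.793 (t distribution, 63 df).
- 66 / (1 − 0.175) = 80, which also matches.

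Every input is an untransformed speed in m/s.

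**2. What a 0.1 m/s gain becomes after transformation.** With g(y) = (y^λ − 1)/λ, or ln y at λ = 0, the table gives g(b + 0.1) − g(b). The starting speeds are illustrative; 0.8 m/s is the eligibility limit.

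| λ | from 0.4 | from 0.6 | from 0.8 |
|---|---|---|---|
| 0 | 0.223 | 0.154 | 0.118 |
| 0.5 | 0.149 | 0.124 | 0.109 |
| 1 | 0.100 | 0.100 | 0.100 |
| 2 | 0.045 | 0.065 | 0.085 |

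Conversely, take one transformed shift worth 0.1 m/s at 0.6. At 0.4 and 0.8 it is worth 0.067 and 0.133 m/s (λ = 0), 0.082 and 0.115 (λ = 0.5), or 0.139 and 0.077 (λ = 2). Only λ = 1 gives a single equivalent in m/s.

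**3. How far λ is likely to move.** The documents do not give the needed population values, so these are assumptions: population mean 0.85 m/s, screening–baseline correlation 0.9, screening speed below 0.8, exactly normal residuals, a true effect of 0.1 m/s, and 66 participants. SD 0.24 and correlation 0.8 are the plan's.

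- In 2,000 simulated trials, fitted λ ran from 0.53 to 1.69 (5th to 95th percentile).
- A separate run of the scenario put the raw coefficient at about 0.80 to 1.18 times the m/s effect (same percentiles).
- Power with and without Box-Cox was 78.0% and 78.2% in one run, and 78.8% and 79.3% in another.

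**4. Whether the transform is needed to protect the test.** With 33 per arm and 10,000 runs each, untransformed ANCOVA had type I error 0.050 with normal residuals and 0.047 with strongly skewed (exponential) residuals. The exponential shape is an assumption.

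**5. Zeros.** The Box-Cox log-likelihood contains (λ − 1) Σ ln y, which has no finite value when any y is 0 (except trivially at λ = 1). Four zeros were added to 66 simulated speeds (assumed mean 0.65, SD 0.20). The standard fitting routine refused the data, and the log-likelihood was infinite or undefined at every λ tried. Adding a constant first makes it run, but λ then depends on the constant: 1.07, 1.26, 1.58 and 2.81 for shifts of 0.001, 0.01, 0.1 and 1. With λ held fixed and positive, the transform of 0 is finite: −1/λ, for example −2.0 at λ = 0.5.

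**The case against.** The strongest reply is that the plan tests superiority against no difference, and a monotone transform leaves that test meaningful. Fitted values can be back-transformed to m/s. In simulation under the assumptions above, the back-transformed difference at mean baseline averaged 0.099 to 0.0995 m/s against a true 0.1, and in 95% of trials it was within 0.008 m/s of the untransformed estimate. Reporting scale, triggers and handling of zeros are also details that a condensed article commonly leaves to the analysis plan.

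Much of this stands, and it rules out several stronger readings that a reader might infer:

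- *Box-Cox is mandatory.* It is given only as an example, and the family includes λ = 1, which leaves the m/s scale intact.
- *The result can never be compared with 0.1 m/s.* Back-transformation at chosen covariate values would allow it; the article simply does not plan it.
- *Imputed zeros break the primary analysis.* That analysis is complete-case. Zeros enter only conditional sensitivity analyses, and fail there only if λ is zero or negative or is re-estimated without a shift.
- *The trial would not answer its question.* The stated question is superiority. No section sets a test against 0.1 m/s.
- *The 0.8 m/s eligibility cut will make outcomes look non-normal.* In the same scenario, a Shapiro–Wilk test rejected normality of the 4-month speeds in 5.3% to 5.9% of trials, about the nominal 5%. The cut applies to screening speed.

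Deferral to the analysis plan does not dispose of the point. The article is not silent: it commits to a transform and draws the primary estimate from it. A plan that followed this wording would inherit the mismatch, and one that analysed m/s would depart from it.

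**Conclusion.** The point holds as a mismatch of scale. The outcome, MCID, SD and power are in m/s, while the primary estimate and CI are to come from an unconditional, data-chosen transform with no stated route back. Under the assumed population values, the raw coefficient would typically lie within about 20% of the m/s effect in either direction. The larger distortions at λ = 0 or 2 illustrate the mechanism and lie outside the simulated range of λ. The transform brings no visible gain in power, and the skewed-residual check suggests that it is not needed to control type I error. The p value for superiority is not in question. The zero-value conflict is real but confined to conditional sensitivity analyses. Severity: should-fix. The simulated sizes rest on the assumed mean and screening–baseline correlation; the algebra of the scale does not.

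**What to change.** Make the regression of untransformed 4-month walk speed on arm, baseline walk speed and sex the primary analysis. Report the adjusted mean difference in m/s with its 95% CI alongside the 0.1 m/s MCID. Check the residuals, and use robust (such as HC3) or bootstrap intervals if they are clearly non-normal or heteroscedastic. Keep any transformed analysis as a sensitivity analysis, judged on residuals and not applied to data containing imputed zeros; run the worst-score analyses in m/s. Carry the same wording to the continuous secondary endpoints, each in its own units.

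The cost is a change of wording in the protocol and analysis plan. Robust standard errors may be slightly wider or less familiar where they are used. The sample size stays at 66 evaluable and 80 recruited, because it was derived on the m/s scale.
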